#### Secondary outcome: standardized measurement of health status via EuroQol (EQ-5D) and WHOQOL-BREF

Another secondary outcome will be the assessment of the health status of participants, as measured by the EQ-5D. This instrument is a non-disease-specific self-report of health-related quality of life. It is applicable to a wide range of health conditions and treatments, and provides a simple measurement of health that is used in clinical and economic analysis. Each respondent defines his/her own health status by combining one level (from a choice of three: “no problems”, “some problems”, “extreme problems”) from each of five dimensions: mobility; self-care; usual activities; pain/discomfort; and anxiety/depression. For any state of health reported, an EQ-5D score reflecting a health utility weight will be derived.

Quality of life will also be assessed using the WHOQOL-BREF — an instrument developed by the World Health Organization. It is a 26-item Likert scale, which focuses on four aspects of quality of life: physical health, psychological health, social relationships, and environment. It also contains two items concerning the individual’s overall satisfaction with life and general sense of personal well-being. Each response on this Likert scale is coded from 1 to 5.

To complement the assessment of the health status of participants, we will address patient satisfaction through a five-item questionnaire, validated locally.

#### Secondary outcome: feelings of discrimination

Additionally, an instrument assessing the feelings of discrimination will be filled in by each participant at the beginning of the study and 12 months later. The discrimination instrument was validated in a previous study conducted at the University Hospital of Geneva [53].

### Sample size

The sample size has been calculated to detect a between-group average reduction of two visits per year to the ED (i.e. minus four visits for the intervention group versus minus two for the control, with an expected standard deviation of four in both groups), in accordance with the results of a systematic review of the literature by Althaus et al. [32]. With a significance level of 0.05 and power of 0.9, each group should include at least 85 participants. “Given that an increased mortality rate of ED-FUs is described in the literature [54] and that, from previous observations from the CM team’s clinical activities, 30% of our patients should be refugees or undocumented migrants, we expect an increased proportion of patients lost to follow-up. We therefore voluntarily overestimated the drop-out rate for the overall population to be 30% (80/250). The total required sample size has been rounded up to 250 patients (125 in each group).

### Statistical methods

Groups will be compared from their initial allocation independently of eventual crossover (intention-to-treat analyses). The principle measurement of effect is an individual’s average reduction in visits to the ED over 12 months compared to the number of visits observed in the control group. This will be calculated using linear regression with number of visits during 12 months’ follow-up as an independent variable, and group allocation and yearly number of ED visits prior to intervention as dependent variables. Should group imbalance occur, secondary analysis will test the confounding effects by measuring the effect after adjusting for these confounding effects in the linear regression. Known determinants of frequent use are to be considered as potential confounders if, by chance due to the randomisation, we are to observe a relative difference of 20% between groups.

FUs are known to visit EDs on regular bases over a short period of time [55] (regression to the mean), so we also expect to see a decrease in the number of visits in the control group. Our analysis will measure the true effects of the intervention taking this phenomenon into consideration.

In terms of medico-economic analysis, benefits of the care management program will be evaluated by health gains expressed in Quality Adjusted Life Years (QALYs) over the 12-month period. A cost-utility analysis from the health-care provider perspective will be conducted by combining the use of two outcomes (i.e. costs and health status in terms of quality of life). A cost-utility ratio will then be calculated. A sensibility analysis will also be conducted in order to estimate the confidence interval for the cost-utility ratio. Uncertainty will be assessed by univariate and probabilistic sensitivity analysis (Monte Carlo simulation). All statistical analysis will be carried out with STATA 12.0, Statacorp, College Station, Texas, USA.

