## Discussion

This study is coordinated with recent local research projects dedicated to assessing profiles and improving healthcare for ED-FUs, who are considered to be a highly vulnerable subgroup and a proxy for vulnerable populations in general.

At the Lausanne University Hospital ED, in 2008–2009, ED-FUs accounted for 4.4% of ED patients and 12.1% (n = 5,813) of all ED visits (n = 48,117) [46]. A retrospective chart review case–control study, conducted in this hospital between April 2008 and March 2009 by Bieler et al. [46], demonstrated that social (i.e. homelessness, institutionalization, unemployment, or dependence on government welfare) and specific medical vulnerability factors (i.e. ED primary diagnosis of substance abuse and the use of five or more clinical departments in the 12 previous months) increased the risk of ED use among 719 patients. A combination of social and medical factors was markedly associated with frequent ED use, as FUs were 10 times more likely to have three of them (of a total of eight factors; 95% CI = 5.1 to 19.6). This result is confirmed by Althaus et al. [56] in a retrospective chart review on hyperfrequent users (12 attendances or more during a year): they were 13 times more likely than non-FUs (65.5 vs 5.0%) to present three or more of the risk factors of vulnerability that Bieler et al. referred to [46] and 2.2 times more likely than FUs (62.5 vs 28.4%). Finally, unpublished, local, prospective, cross-sectional data ([name] et al., in progress) obtained between November 2009 and June 2010 has demonstrated differences between 226 FUs and 173 infrequent users. FUs were more often younger with a mean age of 51 vs 56 in infrequent users, and the former had experienced five to 18 admissions in the previous 12 months. They cumulated vulnerabilities in terms of somatic problems, mental diseases, risk behavioral indicators, and unfavorable social determinants of health.

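### The covariates of the secondary adjusted analysis are chosen by an observed 20% relative difference, a trigger set by prevalence and coding and not by prognostic strength

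*Protocol article*

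**What the plan says.** All of this is in the Statistical methods section of the protocol article.

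- **Primary model.** A linear regression of 12-month ED visits, with "group allocation and yearly number of ED visits prior to intervention as dependent variables". The labels for outcome and predictors are swapped in that sentence, but the meaning is clear: prior-year visits are in the model unconditionally.
- **Secondary model.** "Should group imbalance occur, secondary analysis will test the confounding effects by measuring the effect after adjusting". It is run only if imbalance is seen.
- **Candidates and trigger.** "Known determinants of frequent use are to be considered as potential confounders", and each of them is "considered as potential confounders if, by chance due to the randomisation, we are to observe a relative difference of 20% between groups".

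The section does not list the determinants at that point or say which group is the denominator of the relative difference. The Discussion reports that a local chart review found "social (i.e. homelessness, institutionalization, unemployment, or dependence on government welfare) and specific medical vulnerability factors" to raise the risk of ED use. The medical factors it gives are a primary ED diagnosis of substance abuse and use of five or more clinical departments in the previous 12 months. It does not link these factors to the 20% rule.

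**The concern.** In a randomised trial every baseline difference is chance. A rule that selects covariates by the observed relative difference therefore selects on noise, and how much noise there is depends on prevalence. For a proportion, the relative difference varies widely when the trait is rare and hardly at all when it is common. How strongly a trait predicts later visits, which is what makes adjustment worthwhile, does not enter the trigger.

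At stake is the adjusted analysis, which is the plan's stated answer to chance confounding. Its covariates would differ from one randomisation to the next for reasons unrelated to prognosis. It could adjust for an imbalance that hardly moves the estimate and pass over one that does. Any precision to be had from a prognostic covariate that happens to look balanced is lost.

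**Working it through.** **Inputs.** 125 randomised per group, 85 per group needed before drop-out, effect of 2 visits, SD 4, alpha 0.05, power 0.9 (Sample size). 20% relative difference (Statistical methods). Mean age 51 in frequent users, and 28.4% of them with three or more vulnerability factors (Discussion). Assumed, because the article does not give them: prevalences of 5% to 80%, an age SD of 15 to 20 years, a covariate effect of 2 visits, and covariate R² of 0.05 to 0.20.

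**1. The plan's own figure.** The design is to "detect a between-group average reduction of two visits per year to the ED", "with an expected standard deviation of four in both groups". Two-sided, n per group = 2 × (1.960 + 1.282)² × 4² / 2² = 84.06, rounded up to 85. This reproduces "With a significance level of 0.05 and power of 0.9, each group should include at least 85 participants". The 20% rule itself comes with no stated operating characteristic.

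**2. Chance of triggering under correct randomisation.** Let A and B be independent Binomial(n, p) counts. The exact probability is the sum of P(A = a) × P(B = b) over all pairs that meet the rule, exact 20% ties included. Two readings of the denominator bracket the rule: larger/smaller ≥ 1.20, and (larger − smaller)/larger ≥ 0.20. Taking the control group as denominator falls between them.

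| Prevalence | n = 125, smaller group as denominator | n = 125, larger group as denominator | n = 85, smaller group as denominator |
|---|---|---|---|
| 5% | 77% | 72% | 83% |
| 10% | 65% | 58% | 71% |
| 20% | 48% | 39% | 57% |
| 28.4% | 37% | 28% | 47% |
| 30% | 36% | 26% | 45% |
| 50% | 16% | 8% | 24% |
| 70% | 3% | 0.8% | 7% |
| 80% | 0.5% | 0.06% | 2% |

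**3. Coding.** A trait held by 20% of patients triggers 48% of the time. Recorded as its absence (80%), the same data trigger 0.5% of the time.

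**4. A continuous covariate.** For age, 20% of 51 is 10.2 years. The SE of the difference is SD × √(2/125), which is 1.90 years at SD 15 and 2.53 at SD 20. So z is 5.38 or 4.03, and the chance of triggering is at most about 6 in 100,000.

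**5. What an imbalance at the threshold does.** The shift in the unadjusted estimate is about 0.20 × p × covariate effect. The SE of the treatment difference is 4 × √(2/125) = 0.506. With an assumed effect of 2 visits:

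- p = 5%: 0.20 × 0.05 × 2 = 0.02 visits, or 0.04 of the SE
- p = 50%: 0.20 × 0.50 × 2 = 0.20 visits, or 0.40 of the SE
- p = 80%: 0.20 × 0.80 × 2 = 0.32 visits, or 0.63 of the SE

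The trigger is easily reached where imbalance matters least and hardly ever reached where it matters most.

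**6. Type I error.** In 20,000 simulated null trials for each of five settings, with one binary covariate and 125 per group, adjusting only when triggered rejected in 4.4% to 5.0%. Always adjusting rejected in 5.0% to 5.1%.

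**7. Precision.** With a prespecified covariate set, n for 90% power is 84.06 × (1 − R²). At an assumed R² of 0.05, 0.10 or 0.20, the requirement falls from 85 to 80, 76 or 68 per group.

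**The case against.** Four points on the other side are sound and limit the concern.

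- **Candidates are already screened.** The rule applies only to known determinants of frequent use. A reader might infer that the plan would adjust for variables unrelated to ED use. The text does not support that: association with frequent use is the entry condition, and only its strength is ignored at the trigger.
- **Prior-year visits are always adjusted for.** A reader might infer that nothing is adjusted for unless an imbalance appears. That is wrong for what is plausibly the strongest predictor.
- **The analysis is secondary.** The primary estimate and its error rate do not depend on the rule, and the simulations show no inflation even when the triggered model is used for the test. The threshold is numerical, and the Blinding section keeps the statistician blind to the true group until the analyses are complete, so there is little room to steer the result.
- **A covariate list may sit in an analysis plan that is not shown.** Its absence from the article is no fault. The objection here is to the trigger, which the article does state.

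It would also go too far to say that the rule would miss a prognostically important age gap of a few years. The Discussion compares the ages of frequent and infrequent users (51 and 56). It says nothing about age predicting visits among frequent users. For the same reason, the strength of the Discussion's other factors within this trial is inferred, since they come mainly from comparisons with patients who are not frequent users.

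None of this defends the 20% relative difference as a way to choose covariates.

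**Conclusion.** The concern holds for the secondary adjusted analysis and no further. Which known determinants enter that model is decided by chance, at rates from about 77% for a trait with 5% prevalence to 0.5% for one with 80% (72% to 0.06% with the other denominator). The recoding of a single trait can reverse the outcome. The primary estimate stands, the sample size calculation is sound, and alpha is not at issue.

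The trigger probabilities rest only on equal groups of 125 and correct randomisation. With 85 per group they are higher, with the same pattern. The shifts in the estimate and the gains in precision rest on assumed covariate effects and R², and show direction and order of size only. This is a moderate weakness in a stated rule, worth correcting because doing so is nearly free.

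**What to change.** Delete the 20% trigger. Before unblinding, and before baseline data are tabulated by group, name a short set of covariates collected at baseline and chosen for prognostic value, with the coding of each. Candidates from the Discussion are homelessness, institutionalization, unemployment or welfare dependence, a substance-abuse diagnosis and use of five or more clinical departments. Age could be added. Fit that one secondary model, together with prior-year visits, whatever the observed balance, and report it beside the primary result.

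The cost is a sentence or two and a few degrees of freedom out of 250 patients. New data should not be needed: the baseline assessment described for both groups already covers social determinants, mental and somatic diseases, risk behaviours and health-care use. The team should confirm that each named factor is recorded there or in the hospital databases.

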### Ethical approval

The protocol, information letters, questionnaires, and the informed consent form of the study were approved by the Human Research Ethics Committee of the Canton of Vaud, Switzerland (no 32/12). There is no expected adverse event or side effect for participants.

## Discussion

This study is coordinated with recent local research projects dedicated to assessing profiles and improving healthcare for ED-FUs, who are considered to be a highly vulnerable subgroup and a proxy for vulnerable populations in general.

At the Lausanne University Hospital ED, in 2008–2009, ED-FUs accounted for 4.4% of ED patients and 12.1% (n = 5,813) of all ED visits (n = 48,117) [46]. A retrospective chart review case–control study, conducted in this hospital between April 2008 and March 2009 by Bieler et al. [46], demonstrated that social (i.e. homelessness, institutionalization, unemployment, or dependence on government welfare) and specific medical vulnerability factors (i.e. ED primary diagnosis of substance abuse and the use of five or more clinical departments in the 12 previous months) increased the risk of ED use among 719 patients. A combination of social and medical factors was markedly associated with frequent ED use, as FUs were 10 times more likely to have three of them (of a total of eight factors; 95% CI = 5.1 to 19.6). This result is confirmed by Althaus et al. [56] in a retrospective chart review on hyperfrequent users (12 attendances or more during a year): they were 13 times more likely than non-FUs (65.5 vs 5.0%) to present three or more of the risk factors of vulnerability that Bieler et al. referred to [46] and 2.2 times more likely than FUs (62.5 vs 28.4%). Finally, unpublished, local, prospective, cross-sectional data ([name] et al., in progress) obtained between November 2009 and June 2010 has demonstrated differences between 226 FUs and 173 infrequent users. FUs were more often younger with a mean age of 51 vs 56 in infrequent users, and the former had experienced five to 18 admissions in the previous 12 months. They cumulated vulnerabilities in terms of somatic problems, mental diseases, risk behavioral indicators, and unfavorable social determinants of health.

Taking care of a growing number of vulnerable patients requires specific interventions. A systematic review of the effectiveness of interventions targeting ED-FUs concluded that such interventions may reduce ED use and that CM, the most frequently described intervention, seemed to improve social and clinical outcomes and reduce ED costs in different studies [32]. Three studies [12,29,31], from which one RCT [29], concluded that CM could contribute to the reduction of ED use and of consequent costs, while two of these studies [12,31] found additionaly that CM could also lead to positive social outcomes. However, patterns of care that have succeeded elsewhere have to be tested in local or national settings before being introduced into a new context of care among local patients. A mixed methodology using quantitative and medico-economic analysis is needed.

Responding to the knowledge gaps in the literature [57,58] and following our local studies through different observational designs, our hypothesis is that CM leads to reduced ED use by ED-FUs through a better orientation in the health-care system, improves their quality of life, and is more cost-effective than is standard emergency care alone provided by nurses and physicians serving ED-FUs. Positive findings would constitute a strong incentive to replicate these studies on a larger scale, in a multicenter study with more extensive follow-up procedures. Positive findings would also suggest that specific populations need specific care, and would have major implications for healthcare quality and costs. Finally, the total number of ED visits in Switzerland is around 1.3 million per year [59] and has been steadily growing. If our intervention results in a reduction in the number of ED visits, the impact at the national level could be significant.

## Abbreviations

RCT: Randomised controlled trial; ED: Emergency department; FU: Frequent user; ED-FU: Emergency department frequent user; CM: Case management; GP: General practitioner.
